## Drug product

**DC/LNCAP:** Autologous dendritic cells which have been exposed to apoptotic LNCAP cells.

**DC/LNCAP-M1:** Autologous dendritic cells which have been exposed to apoptotic LNCAP cells that are stably transfected with a plasmid cDNA expressing the influenza matrix antigen.

**DC/KLH:** Autologous dendritic cells which have been exposed to KLH.

### Components

**Autologous DCs:** Autologous DCs are prepared from leukapheresis of prostate cancer patients entered into the clinical trial.

**LNCaP tumor cells:** The LNCaP prostate tumor cell line was obtained from the ATCC (clone FCG, catalog No. CRL-1740). These cells were maintained throughout growth in our laboratory in defined media, with careful documentation since their arrival in the laboratory. This initially consisted of sterile DMEM (Cell-GRO cat # 10-013-CV) plus 10% USA BSE-free fetal calf serum (FCS) (HyClone cat # SH30071.03, lot # ALA13021). Cells were subsequently weaned to the lowest possible dose of BSE-free FCS, which was 1% in Aim V media, and were subsequently maintained in that state. Frozen stocks were made in Aim V media (Gibco-BRL cat # 12055-091, Lot# 1106795) plus 20% BSE-free FCS and 5% DMSO (Sigma Cat # D2650 Lot# 71K2402).

**Other Reagents:** See Appendix I. Certificates of analysis are available for all reagents that will be used in clinical trial.

### Quantitative composition of Drug Product

DC/LNCaP cells from co-cultured purified components (DC and apoptotic LNCaP cells). Co-cultures will be done at a ratio of one apoptotic LNCAP cell to one autologous DC, determined by the numbers of available LNCaP and DCs. Cells are co-cultured for 30-48 hours and frozen in 5% DMSO, 25% autolgous serum. Aliquots are frozen at a cell concentration of 1-4 x 107 cells/ml.

Aliquots will be thawed, and 2-10 x 106 DCs will be injected.

### Qualitative composition of Drug Product

Quality of the DC/LNCAP product was demonstrated in human cells *ex vivo*. DC/LNCAP cells were prepared as above, except that LNCAP cells were infected with influenza virus to deliver the M1 antigen to these cells prior to induction of apoptotic death. Alternatively, DC/LNCAP-M1 cells were used as immunogen ex vivo. Human cells used to produce DCs were either obtained from normal volunteers or prostate cancer patients. In both instances, DCs of ~ 90% purity were generated, as determined by flow cytometric analysis of DC-specific cell markers. Both normal individuals and prostate cancer patients cells were able to mount antigen-specific CD4+ and CD8+ T cell responses DC/LNCAP and DC/LNCAP-M1 cells, as assessed by ELISPOT or CTL assay (see (8).iii).

### Manufacturing/packaging procedure

##### Drug Formulation and Route of Administration

DC/LNCAP or DC-LNCAP/M1 are suspended in 5% DMSO and 25% autologous serumin sterile saline at a concentration of 1-4 x 107 cells (DCs)/ml. 2-10 x 106 cells are injected (0.5 ml) subcutaneously.

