### Vaccines

**DC/LNCAP:** Autologous dendritic cells that have been co-cultured with apoptotic LNCAP cells.

**DC/LNCAP-M1:** Autologous dendritic cells that have been co-cultured with apoptotic LNCAP-M1 cells that are stably transfected with a plasmid cDNA expressing the influenza matrix antigen.

**DC/KLH:** Autologous dendritic cells that have been exposed to KLH.

**Lot numbers**: 02-A1 to 03-A24

**Dose concentration**: 2-10 x 106 DC/LNCaP per injectate, 2-10 x 106 DC/LNCaP-M1 or 2-10 x 106 DC/KLH per injectate. Cells are resuspended in 0.5 ml 5% DMSO and 25% autologous serum in sterile saline for injection.

**Route of administration**: Cells will be injected into the subcutaneous tissue of the upper arm or thigh with a tuberculin syringe.

**Placebo**: either saline or vaccine vehicle only (5%DMSO in sterile saline.

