## Labeling

Copies of all labels to be provided to investigators are shown below.

Patient Name:

Autologous DC/LNCaP vaccine in 5% DMSO and 25% autologous serum in sterile saline

2 - 10 x 106 autologous dendritic cells/0.5 ml. Store at 2-8oC

CAUTION: NEW DRUG LIMITED BY FEDERAL LAW TO INVESTIGATIONAL USE; NOT EVALUATED FOR INFECTIOUS SUBSTANCES; FOR AUTOLOGOUS USE ONLY

Rockefeller University Hospital GCRC

Lot: _______Patient ID#_________ Investigator:______________

Patient Name:

Autologous DC/LNCaP-M1 vaccine in 5% DMSO and 25% autologous serumin sterile saline

2 - 10 x 106 autologous dendritic cells/0.5 ml. Store at 2-8oC

CAUTION: NEW DRUG LIMITED BY FEDERAL LAW TO INVESTIGATIONAL USE; NOT EVALUATED FOR INFECTIOUS SUBSTANCES; FOR AUTOLOGOUS USE ONLY

Rockefeller University Hospital GCRC

Lot: ______ Patient ID#_______ Investigator: _______________

Patient Name:

Autologous DC/KLH vaccine in 5% DMSO and 25% autologous serum in sterile saline

2 - 10 x 106 autologous dendritic cells/0.5 ml. Store at 2-8oC

CAUTION: NEW DRUG LIMITED BY FEDERAL LAW TO INVESTIGATIONAL USE; NOT EVALUATED FOR INFECTIOUS SUBSTANCES; FOR AUTOLOGOUS USE ONLY

Rockefeller University Hospital GCRC

Lot: ______Patient ID# ____________ Investigator: _____________

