# Pharmacology/Toxicology information

## Safety studies

### Animal studies to evaluate drug toxicity

Toxicity of LNCAP cells was assessed in animals to assess whether any LNCaP cells remain viable following the protocol we will use to induce apoptotic death.

We assessed the ability of LNCaP prostate cancer cells to grow in SCID and *nude* mice. Both of these strains are immunoincompetent and thereby provide means of monitoring tumor cell survival. Injection of 5 x 107 apoptotic cells in Matrigel into SCID and *nude* mice produced no evidence of tumor growth after 42 days, while as few as 10 living tumor cells grew into detectable tumors within 21 days following injection (see Figure 4).

Toxicity of DC/LNCaP cells was assessed in animals. Live autologous bone-marrow derived DCs were harvested and differentiated in vitro using GM-CSF for seven days. These cells were then co-cultured with apoptotic LNCaP cells (ratio of 1:1) in the presence of TNF-a and PGE2 for 40 hours. These DC/LNCaP cells were injected into the footpad of 6-8 week old C57BL/6 and BALB/c mice at concentrations of 104, 105, and 106. To attempt to provoke dose-limiting toxicities, mice treated with 106 DC/LNCaP cells were also given an extra vaccination (5 instead of 4 injections) in an accelerated schedule (weekly instead of every other week). Following the last vaccination, mice were sacrificed to perform histological and clinical laboratory (complete blood count and either ANA or dsDNA) examinations. Serum chemistries were also assessed in mice that received 104 and 105 cells. Histologic studies were performed blindly on each group by an independent licensed veterinary pathologist (IDEXX). In each case, results were compared with those of control mice that had been injected with PBS.

The DC/LNCaP cell doses used in these studies correspond, on a live DC cell number/body weight basis, to an excess of approximately 3-fold, 30-fold, and 300-fold, for cell doses of 104, 105, and 106 cells, respectively, relative to the maximum dose (10 x 106 DC/LNCaP cells/injection) to be used in clinical study.

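### The injectate specification contradicts itself: 0.5 ml at the stated 1–4 × 10^7 cells/ml holds 5–20 × 10^6 cells, not the stated dose of 2–10 × 10^6

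*Combined protocol and SAP*

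**What the plan says.** Section (7)v.e, Drug Formulation and Route of Administration, describes DC/LNCaP and DC/LNCaP-M1 as suspended in DMSO, autologous serum and saline "at a concentration of 1-4 x 107 cells (DCs)/ml. 2-10 x 106 cells are injected (0.5 ml) subcutaneously". The lost superscripts come from text extraction: 107 is 10^7 and 106 is 10^6.

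Other sections repeat the dose and volume but not the concentration:

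- (6)i.f Vaccines gives 2–10 × 10^6 cells per injectate and adds "Cells are resuspended in 0.5 ml 5% DMSO and 25% autologous serum in sterile saline for injection".
- The Dosing Plan in (6)i.g expects 2–10 × 10^6 cells in 0.5 ml, depending on how many cells are available.
- (7)iv.a and (7)iv.b, on preparing DC/LNCaP and DC/LNCaP-M1, have the cells counted and 2–10 × 10^6 of them made up in 0.5 ml. The remainder is then frozen for boosters.
- The labels in (7)viii read "2 - 10 x 106 autologous dendritic cells/0.5 ml".
- (8)i.a computes the animal dose multiples "relative to the maximum dose (10 x 106 DC/LNCaP cells/injection) to be used in clinical study".

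The concentration appears in one other place. Section (7)v.b, Quantitative composition of Drug Product, says "Aliquots are frozen at a cell concentration of 1-4 x 107 cells/ml", and then, without a volume, "Aliquots will be thawed, and 2-10 x 106 DCs will be injected".

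Stability of components, in (7)iii.d, puts initial recovery after thawing at about 50–85%, followed by washing to remove debris. It sets a release criterion of more than 30% survival by comparative cell count.

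**The concern.** A concentration and a volume together fix a cell number. Section (7)v.e gives both and then states a cell number that does not match, at either end of its range. This is the paragraph headed as the drug formulation, so it is where a reader looks for the strength of the injected product.

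The documents say there is no prior human experience with DC/LNCaP or DC/LNCaP-M1, so the strength should be unambiguous. Two other parts of the plan depend on the dose. The animal multiples in (8)i.a are tied to 10 × 10^6 cells per injection. The final analysis described in (6)i.h (Interim and Final Analysis) relates the total number of dendritic cells administered to PSA and to immunologic response, so it should be clear which count is meant by the number administered.

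**Working it through.** **Inputs.** Concentration 1–4 × 10^7 cells/ml, from (7)v.e and, as a freezing concentration, (7)v.b. Volume 0.5 ml, from (7)v.e, (6)i.f, the Dosing Plan, (7)iv.a, (7)iv.b and (7)viii. Dose 2–10 × 10^6 cells, from the same sections. Recovery 50–85%, from (7)iii.d.

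**Step 1: the formulation paragraph as written.** Cells = concentration × volume.

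- Low end: 1 × 10^7 × 0.5 = 5 × 10^6, which is 2.5 times the stated minimum of 2 × 10^6.
- High end: 4 × 10^7 × 0.5 = 20 × 10^6, which is 2.0 times the stated maximum of 10 × 10^6.

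The stated dose range is not reproduced. The computed range (5–20 × 10^6) and the stated range (2–10 × 10^6) share only 5–10 × 10^6.

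**Step 2: the concentration implied by dose and volume.** Concentration = dose / volume.

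- 2 × 10^6 / 0.5 ml = 0.4 × 10^7/ml.
- 10 × 10^6 / 0.5 ml = 2 × 10^7/ml.

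So 2–10 × 10^6 cells in 0.5 ml means 0.4–2 × 10^7/ml, against the stated 1–4 × 10^7/ml. The overlap is 1–2 × 10^7/ml.

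**Step 3: the volume implied by dose and concentration.** Volume = dose / concentration.

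- 2 × 10^6 cells occupy 0.2 ml at 1 × 10^7/ml and 0.05 ml at 4 × 10^7/ml.
- 10 × 10^6 cells occupy 1.0 ml at 1 × 10^7/ml and 0.25 ml at 4 × 10^7/ml.

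No section gives an injected volume for these products other than 0.5 ml.

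**Step 4: can post-thaw loss explain the difference?** Suppose 1–4 × 10^7/ml is the pre-freeze concentration and 0.5 ml of stock is thawed. Cells = concentration × 0.5 ml × recovery.

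| Recovery | At 1 × 10^7/ml | At 4 × 10^7/ml |
| --- | --- | --- |
| 50% | 2.5 × 10^6 | 10 × 10^6 |
| 85% | 4.25 × 10^6 | 17 × 10^6 |

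At 50% recovery the result lies inside the stated dose range and nearly spans it. The top end equals 10 × 10^6 only when recovery is 10/20 = 50%, and any higher recovery takes it above. The wash that follows thawing may lose further cells, but the documents do not say how many.

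**Step 5: the animal multiples.** Assume a mouse of 20–25 g and a man of 70 kg; the documents give neither weight. The lowest mouse dose gives (10^4 / 0.020–0.025 kg) / (10 × 10^6 / 70 kg) = 2.8–3.5, in line with the stated 3-fold. The 30- and 300-fold figures follow by factors of ten. These multiples agree with the maximum that (8)i.a states.

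**The case against.** The strongest reply is that 1–4 × 10^7/ml is simply the stock concentration. Section (7)v.b says so for frozen aliquots. The formulation paragraph sits under a manufacturing and packaging heading, and it can be read as a packaged strength followed by an injected dose. The preparation sections set the injectate by counting cells and making up the counted number in 0.5 ml, so 2 × 10^6 cells can be delivered in that volume without any conflict. At 50% recovery the stock figures nearly reproduce the stated range.

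Much of this stands. It is the likeliest explanation, and the conflict lies in the concentration clause alone, because the dose and volume in (7)v.e match the other sections. It does not repair the text, however. The paragraph does not mention freezing or dilution. The vehicle does not separate stock from injectate, since both are described with 5% DMSO and 25% autologous serum. The count in (7)iv.a and (7)iv.b comes before the boosters are frozen, and no section describes bringing thawed cells to 0.5 ml. Recovery closes the gap only at the low end of its stated range.

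A reader might go further and infer that patients could be given 20 × 10^6 cells, that low-yield patients could not be dosed in 0.5 ml, or that the animal multiples are overstated by a factor of two. The documents do not support this. No section states a dose of 20 × 10^6; the same paragraph, the label and (8)i.a all keep to 10 × 10^6 or below; and the multiples agree with that maximum. Nor is the planned dose-response analysis shown to be wrong, because it uses cells administered rather than a nominal concentration times a volume.

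**Conclusion.** The point holds as a contradiction in the dose specification. Within one paragraph, 0.5 ml at the stated concentration holds 5–20 × 10^6 cells while the stated dose is 2–10 × 10^6, with agreement only over 5–10 × 10^6. The discrepancy is a factor of 2.0 at the top and 2.5 at the bottom. This rests on multiplication alone and needs no outside assumption. That the concentration is a freezing figure carried into the injectate description is an inference from (7)v.b, not something the documents state.

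The size is that of a specification error, not of a demonstrated overdose. No endpoint, sample size or planned test changes. The body weights in Step 5 are assumptions and serve only to show that the animal multiples match the stated maximum. The text should be corrected before the product is prepared from it.

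**What to change.** Reconcile the concentration in (7)v.e, and its relation to the freezing concentration in (7)v.b and the recovery figures in (7)iii.d, with the dose and volume in (6)i.f, the Dosing Plan, (7)iv.a, (7)iv.b, (7)v.e and (7)viii and with the maximum in (8)i.a. After the change, concentration × volume should equal the dose wherever all three appear. Label which concentration applies to the frozen aliquot and which to the injectate, and state the step that links them. State which cell count defines the administered dose, so that the total used in the final analysis is unambiguous.

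The investigators decide which figures stand. The animal multiples in (8)i.a need recalculation only if the reconciled maximum differs from 10 × 10^6 per injection. The cost is a wording change in the manufacturing and dosing sections, with no new tests and no additional patients.

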### Acceptable limits and analytical methods to assure identity, strength, quality, purity

#### Strength and Quality

Identity of LNCaP and LNCaP-M1 cells will be confirmed on the Master Cell line, by both Western blot and FACS analysis.

We will analyze each Master Cell line for PSA expression by Western blot analysis. Controls will include frozen stocks of LNCaP cells from the ATCC that are PSA positive.

We will analyze each Master Cell line for PSA expression and HLA A*0201 surface expression by FACS analysis. Controls will include frozen stocks of LNCaP cells from the ATCC that are PSA positive and HLA A*0201.

Quality of DC/LNCaP, DC/LNCaP-M1, and DC/KLH cells

We will analyze each lot of DC/LNCaP, DC/LNCaP-M1, and DC/KLH cells by FACS analysis prior to cell freezing. Cells will be assessed for DC markers, and should have the following profile (see also (7)iii.d.1): After gating on HLA DR, >70% CD83+, and <15% CD14+.

Aliquots of DC/LNCaP, DC/LNCaP-M1, and DC/KLH cells will be stained for viability with trypan blue and/or propidium iodide. >50% of the cells should exclude trypan blue and/or propidum iodide.

As an additional quality control, we will also intermittently assess the functionality of our frozen-thawed DC/LNCaP, DC/LNCaP-M1 cells. Allo-MLR tests, our primary in vitro assay of DC function, will be performed on DC/LNCaP or DC/LNCaP-M1 cells before and after freezing from cells obtained from our 1st, 2nd, 4th, 8th and 16th patients.

#### Stability

Stability is assessed in frozen/thawed DC/LNCaP preparations.

#### Purity

Purity of the drug product will be assessed by microbiologic testing. Prior to drug release, the following criteria will be met:

- 1. Endotoxin free: less than 5 EU/kg/hr endotoxin, assessed by LAL testing.
  2. Bacteria free: no evidence of bacteria by Gram Stain.
  3. Mycoplasma free: no evidence of mycoplasma by PCR test or fluorochrome test.

In addition, priority of the final drug product will be assessed by microbiology testing for sterility. These results will not be available at the time of drug injection, but will be monitored for each injectate.

## Lot release summary.

### Lot release tests.

Aliquots of master cell lines of LNCaP and LNCaP-M1 cells will be assessed for purity by testing for adventitious agents by BioReliance. In addition, an aliquot of LNCaP and LNCaP-M1 master cell lines will be confirmed as PSA and HLA A*0201 positive by FACS, and PSA and PSMA positive by Western blot.

The final product—DC/LNCaP, DC/LNCaP-M1 or DC/KLH cells—are assessed for sterility and purity prior to injection, as summarized in Table 4 below.

Table 4: Lot Release Summary

| **Components** | **Tests Performed** | **Results** | **Acceptable Limit** |
| --- | --- | --- | --- |
| LNCaP | Microbiologic testing  Endotoxin testing | No growth  <1 EU/kg/hr | no bacterial, mycoplasma or fungal growth  < 5 EU/kg/hr |
| DC | Microbiologic testing  Endotoxin testing | No growth  <1 EU/kg/hr | no bacterial, mycoplasma or fungal growth  < 5 EU/kg/hr |
| DC/LNCaP | Microbiologic testing  Endotoxin testing | No growth  <1 EU/kg/hr | no bacterial, mycoplasma or fungal growth  < 5 EU/kg/hr |
|  | Viability | 75-95% | > 50% thawed cells exclude trypan blue or PI |
|  | Identity | 85-98% DCs | > 70% DCs by FACS |
| DC/LNCaP-M1 | Microbiologic testing  Endotoxin testing | No growth  <1 EU/kg/hr | no bacterial, mycoplasma or fungal growth  < 5 EU/kg/hr |
|  | Viability | 75-95% | > 50% thawed cells exclude trypan blue or PI |
|  | Identity | 85-98% DCs | > 70% DCs by FACS |
| DC/KLH | Microbiologic testing  Endotoxin testing | No growth  <1 EU/kg/hr | no bacterial, mycoplasma or fungal growth  < 5 EU/kg/hr |
|  | Viability | 75-95% | 50% thawed cells exclude trypan blue or PI |
|  | Identity | 85-98% DCs | > 70% DCs by FACS |

## Placebo Identity

### Description of placebo

5% DMSO and 25% autologous plasmain sterile saline will be injected (0.5 ml) subcutaneously.

## Labeling

Copies of all labels to be provided to investigators are shown below.

Patient Name:

Autologous DC/LNCaP vaccine in 5% DMSO and 25% autologous serum in sterile saline

2 - 10 x 106 autologous dendritic cells/0.5 ml. Store at 2-8oC

CAUTION: NEW DRUG LIMITED BY FEDERAL LAW TO INVESTIGATIONAL USE; NOT EVALUATED FOR INFECTIOUS SUBSTANCES; FOR AUTOLOGOUS USE ONLY

Rockefeller University Hospital GCRC

Lot: _______Patient ID#_________ Investigator:______________

Patient Name:

Autologous DC/LNCaP-M1 vaccine in 5% DMSO and 25% autologous serumin sterile saline

2 - 10 x 106 autologous dendritic cells/0.5 ml. Store at 2-8oC

CAUTION: NEW DRUG LIMITED BY FEDERAL LAW TO INVESTIGATIONAL USE; NOT EVALUATED FOR INFECTIOUS SUBSTANCES; FOR AUTOLOGOUS USE ONLY

Rockefeller University Hospital GCRC

Lot: ______ Patient ID#_______ Investigator: _______________

Patient Name:

Autologous DC/KLH vaccine in 5% DMSO and 25% autologous serum in sterile saline

2 - 10 x 106 autologous dendritic cells/0.5 ml. Store at 2-8oC

CAUTION: NEW DRUG LIMITED BY FEDERAL LAW TO INVESTIGATIONAL USE; NOT EVALUATED FOR INFECTIOUS SUBSTANCES; FOR AUTOLOGOUS USE ONLY

Rockefeller University Hospital GCRC

Lot: ______Patient ID# ____________ Investigator: _____________

## Environmental analysis requirement

Exempt § 25.31(e).

# Pharmacology/Toxicology information

## Safety studies

### Animal studies to evaluate drug toxicity

Toxicity of LNCAP cells was assessed in animals to assess whether any LNCaP cells remain viable following the protocol we will use to induce apoptotic death.

We assessed the ability of LNCaP prostate cancer cells to grow in SCID and *nude* mice. Both of these strains are immunoincompetent and thereby provide means of monitoring tumor cell survival. Injection of 5 x 107 apoptotic cells in Matrigel into SCID and *nude* mice produced no evidence of tumor growth after 42 days, while as few as 10 living tumor cells grew into detectable tumors within 21 days following injection (see Figure 4).

Toxicity of DC/LNCaP cells was assessed in animals. Live autologous bone-marrow derived DCs were harvested and differentiated in vitro using GM-CSF for seven days. These cells were then co-cultured with apoptotic LNCaP cells (ratio of 1:1) in the presence of TNF-a and PGE2 for 40 hours. These DC/LNCaP cells were injected into the footpad of 6-8 week old C57BL/6 and BALB/c mice at concentrations of 104, 105, and 106. To attempt to provoke dose-limiting toxicities, mice treated with 106 DC/LNCaP cells were also given an extra vaccination (5 instead of 4 injections) in an accelerated schedule (weekly instead of every other week). Following the last vaccination, mice were sacrificed to perform histological and clinical laboratory (complete blood count and either ANA or dsDNA) examinations. Serum chemistries were also assessed in mice that received 104 and 105 cells. Histologic studies were performed blindly on each group by an independent licensed veterinary pathologist (IDEXX). In each case, results were compared with those of control mice that had been injected with PBS.

The DC/LNCaP cell doses used in these studies correspond, on a live DC cell number/body weight basis, to an excess of approximately 3-fold, 30-fold, and 300-fold, for cell doses of 104, 105, and 106 cells, respectively, relative to the maximum dose (10 x 106 DC/LNCaP cells/injection) to be used in clinical study.

There was no clinical toxicity evident in any of the treated or PBS control animals. Only three reproducible differences in the types of histologic changes seen at necropsy were observed between the PBS injected group and the DC/LNCaP cell injected groups. In mice treated with 105 and 106 DC/LNCaP cells, evidence of inflammation (synovitis or granuloma formation) were evident in the footpads of a significant number of DC/LNCaP injected mice compared to PBS injected mice. In mice given the 106 DC/LNCaP vaccine regimen, inguinal lymphadenitis was consistently seen in the lymph nodes that drained the footpad where vaccine was injected. Finally, in given the 106 DC/LNCaP vaccine regimen, there was evidence of vascular inflammation in the lungs of treated mice. These results are summarized in Table 5, and the formal pathology reports on all mice are included in the Appendix.

Analysis of serum ANA levels revealed that mice treated with 106 DC/LNCaP cells showed an increase in very strongly reactive ANA following injection. No significant differences were seen in the serum chemistry or hematologic profiles of PBS versus DC/LNCaP group other than a mild eosinophilia evident in mice treated with 106 DC/LNCaP cells. The results from all mice are included in the Appendix.

Table 5. Animal Histology Summary

| **DC/LNCaP at 104 and 105 cells injected every 2 weeks for 4 injections in right foot pad assessed at 8 weeks.** | PBS  3 total mice | DC/LNCaP 104  3 total mice | DC/LNCaP 105  3 total mice |
| --- | --- | --- | --- |
| BRAIN | | | |
| No significant changes | 2 | 3 | 3 |
| Meningeal inclusion cyst | 1 | 0 | 0 |
| THYMUS | | | |
| No significant changes | 3 | 3 | 3 |
| HEART | | | |
| No significant changes | 2 | 2 | 2 |
| Myocarditis | 1 | 0 | 0 |
| Valvular melanocytic accumulation | 0 | 1 | 1 |
| LUNG | | | |
| No significant changes | 2 | 2 | 2 |
| Hemorrhage | 1 | 0 | 0 |
| Peribronchiolar lymphoid accumulation | 0 | 1 | 0 |
| Pneumonia | 0 | 0 | 1 |
| LIVER | | | |
| No significant changes | 0 | 0 | 0 |
| Hepatitis | 3 | 3 | 3 |
| Extramedullary hematopoisis | 0 | 1 | 1 |
| KIDNEY | | | |
| No significant changes | 2 | 2 | 3 |
| Proteinuria | 1 | 1 | 0 |
| SPLEEN | | | |
| No significant changes | 0 | 0 | 0 |
| Hemosiderosis | 3 | 3 | 3 |
| SMALL INTESTINE | | | |
| No significant changes | 3 | 3 | 3 |
| LARGE INTESTINE | | | |
| No significant changes | 3 | 3 | 3 |
| RIGHT INGUINAL LYMPH NODE | | | |
| No significant changes | 3 | 3 | 2 |
| Lymphadenitis | 0 | 0 | 1 |
| RIGHT FOOT | | | |
| No significant changes | 2 | 2 | 0 |
| Synovitis | 1 | 1 | 3 |
| LEFT FOOT | | | |
| No significant changes | 3 | 2 | 3 |
| Synovitis | 0 | 1 | 0 |

| **DC/LNCaP at 106 cells injected every 1 week for 5 injections in right foot pad assessed at 6 weeks.** | PBS  3 total mice | DC/LNCaP 106  3 total mice |
| --- | --- | --- |
| BRAIN | | |
| No significant changes | 3 | 3 |
| THYMUS | | |
| No significant changes | 3 | 3 |
| HEART | | |
| No significant changes | 3 | 3 |
| LUNG | | |
| No significant changes | 2 | 0 |
| Hemorrhage | 1 | 0 |
| **Vasculitis** | 0 | 3 |
| LIVER | | |
| Mixed cell infiltration | 3 | 3 |
| KIDNEYS | | |
| No significant changes | 3 | 1 |
| Mononuclear cell infiltration | 0 | 1 |
| Protein Casts | 0 | 1 |
| SPLEEN | | |
| No significant changes | 3 | 3 |
| SMALL INTESTINE | | |
| No significant changes | 3 | 3 |
| LARGE INTESTINE | | |
| No significant changes | 3 | 3 |
| RIGHT INGUINAL LYMPH NODE | | |
| No significant changes | 3 | 0 |
| **Lymphadenitis** | 0 | 3 |
| RIGHT FOOT | | |
| No significant changes | 2 | 0 |
| Inflammation | 1 | 0 |
| Granulomatous inflammation | 0 | 3 |
| LEFT FOOT | | |
| No significant changes | 3 | 3 |

